**Figure 1. F1:**
[figure not shown]
Flowchart of the data collection.

During baseline assessment, basic demographic information (sex, age, body mass index, occupation, distance/time from home to the hospital, insurance type) and clinical information [cardiac arrest type, diagnosis, number of coronary artery stenosis/occlusion, intervention type/result, left ventricular ejection fraction (LVEF) (%), remaining coronary occlusion (%), lipid/glucose profile, echocardiogram findings, risk factor information (diabetes mellitus, hypertension, dyslipidemia, obesity), history of cardiocerebrovascular disease, laboratory results, body composition analysis and physical measurement, cardiopulmonary exercise testing (CPET) results, lifestyle risk factors (smoking, drinking, physical activity)] will be obtained through chart review. Additionally, basic information, patient-reported outcome measures (PROM), and clinical outcomes will be assessed.

At 3 months (assessment after completion of the exercise program), data will be collected on exercise therapy completion rate and the number of session participations.

At 3 and 6 months, body composition analysis, physical measurements, CPET results, PROM, and clinical outcomes will be assessed.

At 12 months, through chart review, echocardiography, laboratory test results, and medical information, if available, will be recorded, and body composition analysis and physical measurements, CPET results, PROM, and clinical outcomes will be assessed.

Patients who discontinue participation in the assessments during the study course will have values used in the analysis until the dropout period. All patients were sent an identical reminder text message informing the participants of the date, time, and location of the upcoming evaluation to promote patient retention and follow-up.

Table 1 presents the details of the data collection.

**Table 1 T1:** Schedule of enrollment, intervention, and assessments.

Timeline assessment item		① Consent	② Baseline	③ Exercise end point 3 months	④ 6 months	⑤ 12 months
Screening		√				
Enroll *		√				
Chart review †	Basic information		√			
	Occupation		√			
	Past history		√			
	Heart disease information		√			
	Cardiovascular imaging and detailed PCI Information		√			
	Echocardiography ‡		√			√
	Lab §		√			√
	Current medication		√			
	Cardiac rehabilitation information		√			
	KASI prior to the onset		√			
Intervention	Incentive		→			

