Subject questionnaire (Assessment Index) ∥	Number of cardiac rehabilitation participation ¶			√		
	Body composition analysis and physical measurement #		√	√	√	√
	CPET results **		√	√	√	√
	KASI, EQ-5D, PHQ-9, and other PROM ††		√	√	√	√
	Clinical outcome §§		√	√	√	√
	Patient questionnaire ∥∥			√		√

CPET = cardiopulmonary exercise testing, EQ-5D = EuroQol 5 dimensions, KASI = Korean activity scale index, PCI = percutaneous coronary intervention, PHQ-9 = patient health questionnaire, PROM = patient-reported outcome measures, VO_2_ = oxygen consumption rate.

* Assignment of research number in order after obtaining consent.

† Chart review through medical records.

‡ Baseline: Preparation of initial trial results during hospitalization, 12-month results recorded if available in the medical record.

§ Baseline: Preparation of initial trial results during hospitalization, 12-month results recorded if available in the medical record.

∥ Questionnaires filled out by actual subjects.

¶ Record of participation in exercise program 36 times.

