### 2.9. Outcome evaluation

#### 2.9.1. Primary outcome.

The primary outcomes at 3 months will be the CR participation rate, defined as the number of CR sessions completed, and the CR completion rate (attendance of sessions greater than 50%; thus, completion of ≥ 18 sessions). Changes in PROM functional status using the Korean activity scale index (KASI), quality of life assessments in EuroQol 5 dimensions, and depression evaluation using the patient health questionnaire will be compared from baseline to 3, 6, and 12 months.

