### 2.11. Statistical analysis

The analysis of this study was performed using an intention-to-treat and per-protocol method. CR participation, defined as the number of sessions completed, will be analyzed as a continuous variable using the student *t* test or Mann–Whitney *U* test, based on the normal distribution of the data. CR completion and categorical variables will be analyzed using chi-square or Fisher’s exact test. Missing data will be replaced using the last observation carried forward or the mean value. In the case of more than 20% of dropouts, missing data in the intent-to-treat analysis will be replaced using multiple imputations. The intention-to-treat population will include all enrolled participants, and the per-protocol analysis will include patients who have completed the 3-month evaluation.

Changes in secondary outcomes over time for the CPET, KASI, EuroQol 5 dimensions, and patient health questionnaire will be analyzed using paired t-tests with comparisons from baseline. Analyses will be conducted for each of the intervention, control, CR completion, and non-completed groups. For non-normal distributions, the Wilcoxon signed-rank test will be used.

Statistical significance will be set at *P* < .05, and SPSS version 20 (IBM SPSS Statistics, New York, NY) will be used for the statistical analysis.

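### The missing-data rule in section 2.11 does not exempt the two attendance outcomes, so mean or multiple imputation could credit sessions that were never attended

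*Protocol article*

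**What the plan says.** Section 2.9.1 defines the first primary outcome as "CR participation rate, defined as the number of CR sessions completed" and the second as attending at least 18 of the 36 sessions. It lists changes in the patient-reported measures in the same paragraph.

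Section 2.11 names the tests for the two attendance outcomes and then says: "Missing data will be replaced using the last observation carried forward or the mean value". It adds: "In the case of more than 20% of dropouts, missing data in the intent-to-treat analysis will be replaced using multiple imputations". No outcome is exempted, and nothing says when the last observation applies and when the mean does, or whether the mean is that of the arm or of the whole sample.

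On the analysis sets, section 2.11 says "The intention-to-treat population will include all enrolled participants" and "per-protocol analysis will include patients who have completed the 3-month evaluation". It does not say which analysis is primary.

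Section 2.8.1 has the number of sessions collected at the 3-month assessment. Table 1 ticks it at that visit only, in the subject-questionnaire block, with the footnote "Record of participation in exercise program 36 times". Section 2.8.1 also says: "Patients who discontinue participation in the assessments during the study course will have values used in the analysis until the dropout period".

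**The concern.** For sessions completed and for completion, stopping early is part of the outcome. A patient who attends 3 sessions and then stays away has a count of 3 and is a non-completer. The value is unknown only if nobody looks it up.

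The plan ties the count to the 3-month visit, and those who stop coming to sessions are probably the ones who miss that visit. If their count is treated as missing, the general rule applies. A mean taken from patients who did return replaces a low count by a higher one. Multiple imputation from the observed counts would tend to do the same.

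Three things are at stake: the estimated effect on the main outcomes, the false-positive rate of the t-test (mean-filled values add patients but no spread), and the meaning of the per-protocol result, which leaves out many of the failures the trial is meant to count.

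**Working it through.** **The plan's own figure.** Inputs from section 2.5: 55.4% vs 15.4%, power 0.8; from section 2.11: alpha 0.05, taken as two-sided. Pooled formula: n = [1.96·√(2·0.354·0.646) + 0.8416·√(0.554·0.446 + 0.154·0.846)]² / 0.400² = (1.3255 + 0.5170)² / 0.16 = 21.2, so 22 per group, as stated. 22/0.9 = 24.4, against 24 stated; this is rounding and not in dispute. The switch to multiple imputation comes at 0.20 × 48 = 9.6, that is from 10 dropouts.

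**What each method does to a session count.**

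- Last observation: a running count carried forward is the number attended, so 0 sessions are credited. The count is scheduled at one visit only, so there is no earlier visit value to carry.
- Mean (illustrative values): if returning incentive patients average 26 sessions and dropouts attended 4, then 2 dropouts gain 2 × 22 = 44 sessions and 4 gain 88. With a control mean of 14, the gains are 2 × 10 = 20 and 4 × 10 = 40.

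**Effect on the mean difference.** The protocol gives no session distribution, so one is assumed. Completers: half at 36, half uniform on 18 to 35 (mean 31.25). Non-completers: uniform on 0 to 17 (mean 8.5). True means:

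- incentive: 0.554 × 31.25 + 0.446 × 8.5 = 21.10
- control: 0.154 × 31.25 + 0.846 × 8.5 = 12.00
- difference: 9.10

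Let dropouts come from those with fewer than 9 sessions (half of the non-completers, mean 4). With a fraction d of the arm lost, own-arm mean filling returns the observed mean, (true mean − 4d)/(1 − d).

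| Share of low attenders lost (incentive / control) | d, incentive | d, control | Observed means | Difference |
|---|---|---|---|---|
| 20% / 40% | 0.446·0.5·0.2 = 0.045 | 0.846·0.5·0.4 = 0.169 | 21.90, 13.63 | 8.3 |
| 40% / 20% | 0.089 | 0.085 | 22.78, 12.74 | 10.0 |

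Overall dropout is about 11% and 9%, close to the plan's 10%. With 40% lost in both arms the difference stays at 9.1. The per-protocol difference equals the observed-mean difference, so it carries the same bias. In simulation, power in the first row falls from about 76% to 72% with own-arm filling and to about 63% per protocol; in the second row own-arm filling raises it to 86%.

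**False-positive rate.** Simulated with 24 per arm, both arms at 15.4%, own-arm mean filling, nominal 5%:

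- distribution above, 40% of low attenders lost in each arm: about 11%
- simpler distribution (completers uniform on 18 to 36), the 2 lowest attenders lost per arm: 9.2%; the 4 lowest per arm: 15.3%; the 4 lowest in one arm only: 17.7%
- true counts: about 5% throughout

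With a pooled mean and equal losses the level stays near 5%, so the inflation depends on which mean is used. The plan does not say. Multiple imputation was not simulated.

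**Completion.** Take 13/24 vs 4/24 true completers (54.2% vs 16.7%, difference 37.5 points), all dropouts being non-completers. Replacing by the observed arm rate gives:

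- 2 lost per arm: 13/22 − 4/22 = 40.9 points
- 4 lost per arm: 13/20 − 4/20 = 45.0 points
- 0 vs 4 lost: 13/24 − 4/20 = 34.2 points

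If instead the imputed mean count is cut at 18, 4 incentive dropouts become completers: 17/24 = 70.8%, and Fisher's p moves from 0.015 to 0.0004. That last step is not in the plan.

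**The case against.** The strongest reply is that the rule covers missing data only. If attendance is known, nothing is missing and the rule is never triggered. Section 2.8.1 points the same way, since using values up to dropout gives the sessions actually attended. The full protocol or analysis plan may state the exemption.

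Much of this stands. A reader might infer that the plan has decided to impute attendance; it nowhere says so. A reader might also infer that carrying the last observation forward credits sessions; on a running count it does not. Nor does section 2.8.1 flatly contradict section 2.11: it fits the last-observation method and conflicts only with the mean and multiple imputation.

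The records are also less certain than they look. Only the experimental arm is paid per session, and Table 1 places the count among the questionnaires, so the source for a control patient who misses the visit is not stated. The patient-reported measures under section 2.9.1 do go missing on dropout, so the argument covers participation and completion only. The per-protocol set accompanies the intention-to-treat analysis and does not replace it.

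The reply does not remove the point. An unrestricted rule follows directly on the tests for the attendance outcomes, the count is tied to a visit that low attenders may miss, and no sentence counts unattended sessions as zero. This is a rule stated too widely, not merely a detail left for later.

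**Conclusion.** The concern holds as a rule that is too wide and is not reconciled with section 2.8.1; it does not hold as a stated decision to impute attendance. It should be fixed, because it touches the main outcomes, but it does not invalidate the design or the sample size.

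Under own-arm mean filling, a true difference of 9.1 sessions becomes about 8.3 or 10.0, according to which arm loses more low attenders. It therefore cannot be called conservative. With no true effect the t-test rejects in about 11% to 18% of runs in the heavier loss patterns, and in 9% when 2 per arm are lost. These sizes rest on assumed session distributions, on dropouts being low attenders, and on the own-arm mean being the one used. The direction of the argument needs only the second of these. The per-protocol set shares the problem, since attending the 3-month evaluation is behaviour after randomisation that is probably tied to attending sessions.

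**What to change.** In section 2.11, state that participation and completion are taken from the session attendance records of both arms for every randomised patient, with unattended sessions counted as 0, fewer than 18 counted as non-completion, and no imputation. Name the record used when a patient misses the 3-month visit. Make this intention-to-treat analysis primary, and label the per-protocol analysis of these two outcomes supportive or descriptive.

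Limit the missing-data rule to exercise testing and the patient-reported measures. Drop single mean imputation there in favour of one prespecified method, for example a mixed model on all observed visits. Align the sentence on discontinuers in section 2.8.1.

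The cost is wording, provided both hospitals log control-arm sessions as they must for the paid arm. The basic sample size stays at 22 per group. All 24 per group then count for attendance, which gives power of 0.849 at 24 against 0.815 at 22 by the pooled formula, if 55.4% and 15.4% are rates among all randomised patients.

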#### 2.9.2. Secondary outcome.

The secondary outcomes at 3 months will be used to assess changes in cardiopulmonary endurance by 1 MET (peak oxygen consumption rate [VO_2_] 3.5 mL/kg/minutes), VO_2_ max, and VO_2_ at the anabolic threshold. At 6 and 12 months, improvement and maintenance of cardiorespiratory endurance by 1 MET (peak VO_2_ 3.5 mL/kg/minutes), VO_2_ max, and VO_2_ at anabolic threshold will be assessed.

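### Replacing missing CPET and questionnaire values by the last observation or the mean either presumes maintenance after the last visit or understates the paired-test standard error

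*Protocol article*

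**What the plan says.** Section 2.11 of the protocol article sets one general rule: "Missing data will be replaced using the last observation carried forward or the mean value". The next sentence limits it: "In the case of more than 20% of dropouts, missing data in the intent-to-treat analysis will be replaced using multiple imputations". That limit names only the intention-to-treat analysis. The other set is defined in the same section: "the per-protocol analysis will include patients who have completed the 3-month evaluation". Patients lost after month 3 therefore stay in the per-protocol set, and no multiple imputation is stated for it.

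The CPET and questionnaire changes "will be analyzed using paired t-tests with comparisons from baseline", within each group, with the Wilcoxon signed-rank test for non-normal data. The level is given as "Statistical significance will be set at *P* < .05".

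Section 2.9.2 states the later CPET objective: "At 6 and 12 months, improvement and maintenance of cardiorespiratory endurance by 1 MET". Section 2.8.1, in the text after Figure 1, adds: "Patients who discontinue participation in the assessments during the study course will have values used in the analysis until the dropout period". Section 2.5 allows for 10% dropout, with 24 participants per group.

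**The concern.** This point concerns the repeated CPET and questionnaire values, not the session count or the completion rate.

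Both rules enter a made-up value into a paired test as if it had been measured. Carry-forward gives a patient last seen at month 3 the month-3 value at months 6 and 12. That patient is counted as having kept the whole gain although nothing was observed after the program ended, and whether gains are kept is the question asked at those visits. A patient lost before month 3 keeps the baseline value and is counted as unchanged.

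Mean filling adds to the sample size while adding too little spread, so the test claims more precision than the data hold. At stake are the 6- and 12-month statements about maintenance and the nominal 5% level of each paired test.

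**Working it through.** **Inputs from the protocol article.** 24 per group and 10% dropout (section 2.5); paired t-test against baseline, 5% level, 20% trigger for multiple imputation (section 2.11); 1 MET = 3.5 mL/kg/min (section 2.9.2). Sidedness is not stated; two-sided is assumed. The article gives no standard deviation, no correlation between baseline and follow-up, no 12-month dropout rate and no expected loss of gain after month 3.

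**The plan's own figure.** The only computed design figure is the sample size. For 55.4% versus 15.4%, two-sided 5%, power 0.8, pooled variance and no continuity correction, the normal approximation gives 22 per group, as stated. It does not bear on missing data. It only supplies the group size: 24 after the dropout allowance.

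**Mean filling.** Let *n* = 24 be the group size and *m* the number observed, with data missing completely at random. The article does not say which mean is meant, so both readings are worked.

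- *Mean change filled.* The sum of squares comes from *m* patients, but the test divides by *n* − 1 and then by *n*. The ratio of reported to correct standard error is sqrt[*m*(*m* − 1) / (*n*(*n* − 1))].
  - *m* = 22: sqrt(462/552) = 0.915
  - *m* = 20: sqrt(380/552) = 0.830
- *Visit mean filled.* The change still varies with the patient's own baseline. The ratio is about sqrt(*m*/*n*), whatever the correlation.
  - *m* = 22: sqrt(22/24) = 0.957
  - *m* = 20: sqrt(20/24) = 0.913

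Paired t-tests were simulated with no true change (100,000 runs per setting; a separate run of 200,000 for the mean-change reading; correlation 0.5 and 0.8 assumed):

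| Filled | Reading | Standard error too small by | Type I error |
|---|---|---|---|
| 2 of 24 (8%) | visit mean | about 4% | 5.7% to 5.9% |
| 2 of 24 (8%) | mean change | 8.5% | 7.1% to 7.3% |
| 4 of 24 (17%) | visit mean | about 9% | 6.9% to 7.2% |
| 4 of 24 (17%) | mean change | 17% | 10.1% to 10.2% |

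For reference, the same test on observed patients only held 4.97% to 5.10%.

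**Carry-forward.** Bias in the group mean = share lost × (value carried − true later value). Assume a true month-3 gain of 3.5 mL/kg/min.

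- *All losses right after month 3, gain later fully lost:* 0.10 × (3.5 − 0) = +0.35 at 10% lost; 0.20 × 3.5 = +0.70 at 20%.
- *Same timing, half the gain lost:* 0.10 × (3.5 − 1.75) = +0.175; 0.20 × 1.75 = +0.35.
- *Same timing, gain kept:* 0.
- *All losses before month 3, half the gain lost:* 0.10 × (0 − 1.75) = −0.175.
- *All losses before month 3, gain kept:* 0.10 × (0 − 3.5) = −0.35.
- *Losses split evenly before and after month 3, half the gain lost:* the two parts cancel to 0.

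In the per-protocol set every patient has a month-3 evaluation, so the early losses that could offset the later ones do not occur there.

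**The case against.** Four points on the other side carry weight.

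First, a reader might infer that every patient lost after month 3 is scored as fully maintained and that both rules always give wrong results. The article does not support that. A patient lost between months 6 and 12 carries the month-6 value, which may already show decline. Above 20% dropout the intention-to-treat analysis moves to multiple imputation. Carry-forward bias is zero if gains persist, and it can be zero or negative when some patients are lost before month 3.

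Second, a reader might infer that section 2.8.1 contradicts section 2.11, with the same value absent under one and filled under the other. That needs the word *only*, which section 2.8.1 does not contain. Its sentence also fits keeping the collected values and then carrying them forward. It is ambiguous, not contradictory.

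Third, error rates of about 7.3% and 10.1% follow only if the mean change is filled. If the visit mean is filled, the excess over 5% with 2 of 24 missing is below 1 percentage point.

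Fourth, the 10% allowance belongs to a sample sized for a 3-month outcome. It does not establish how many patients will be missing at month 12, nor which rule will operate then in the intention-to-treat analysis. Which variable gets which replacement may also be settled in an analysis plan not shown here, so that gap is not counted.

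What remains is that section 2.11 fixes two single-value rules. One presumes the answer to a stated objective for patients last seen at month 3, and the other understates the standard error on either reading of the mean.

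**Conclusion.** The point holds in a limited form. In the intention-to-treat analysis up to 20% dropout, and on the stated text at any dropout level in the per-protocol set, missing CPET and questionnaire values are carried forward or mean-filled.

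The mean-filling part needs no assumption about later decline. The standard error is about 4% to 8.5% too small with 2 of 24 filled and about 9% to 17% with 4 of 24. The type I error is about 5.7% to 7.3% and about 7% to 10% respectively. These figures assume data missing completely at random and a two-sided test, and the visit-mean error rates also assume correlations of 0.5 and 0.8.

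The carry-forward part is a flaw of logic whose size and sign the documents cannot settle. The overstatement of about 0.35 mL/kg/min at 10% lost is an example under assumed conditions, about 0.1 MET (0.35/3.5). At a loss near the planned allowance the distortion is modest, and it grows towards the 20% limit. The session count and completion results are not affected by this point. The rule should be changed, but it does not undermine the trial.

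**What to change.** In section 2.11, drop carry-forward and mean substitution for CPET, KASI, EQ-5D and PHQ-9. Replace them in one of two ways:

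- use the multiple imputation the plan already names at any dropout level and in both analysis sets; or
- analyse all observed visits with a likelihood-based mixed model for repeated measures.

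Carry-forward can stay at most as a labelled sensitivity analysis. In section 2.8.1, state plainly that values observed up to dropout enter the analysis.

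No new patients or data are needed. The cost is slightly more programming and somewhat wider intervals than mean filling would give. The mixed-model option is the larger change: it would also replace the planned paired t-tests, and the Wilcoxon alternative has no direct counterpart in it. Extending the multiple imputation leaves the planned paired t-tests in place.

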### 2.5. Sample size

The sample size was based on the results of a study on providing incentives for CR (e.g., session-completion rate:55.4% vs 29.2%, *P* = .002).^[14]^ However, considering the low CR completion rate in Korea, the session-completion rate was revised to 55.4% versus 15.4% (*P* = .002), and the sample size power was 0.8, thereby requiring 22 subjects for each group. Additionally, considering a 10% dropout rate, 24 participants will be required for each group, resulting in 48 participants. Twenty-four participants (12 each in each group per hospital) will be recruited because this study will be conducted at 2 institutions.

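### The missing-data rule does not exclude the two attendance primary outcomes, so known session counts can be replaced by a mean or an imputed value

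*Protocol article*

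**What the plan says.** Section 2.11 gives the tests for both attendance outcomes first. For the count: "CR participation, defined as the number of sessions completed, will be analyzed as a continuous variable". Completion, defined in Section 2.9.1 as "attendance of sessions greater than 50%; thus, completion of ≥ 18 sessions", is compared by chi-square or Fisher's exact test. The next sentence of the same paragraph is the missing-data rule, "Missing data will be replaced using the last observation carried forward or the mean value", followed by "In the case of more than 20% of dropouts, missing data in the intent-to-treat analysis will be replaced using multiple imputations". The paragraph ends by defining the intention-to-treat set as everyone enrolled and the per-protocol set as those with a 3-month evaluation. The exercise-test and questionnaire outcomes appear only in the paragraph after that.

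Section 2.8.1, in the text after Figure 1, has a different rule: "Patients who discontinue participation in the assessments during the study course will have values used in the analysis until the dropout period".

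Table 1 lists "Number of cardiac rehabilitation participation" under the subject questionnaire and ticks it at 3 months only. Its footnote describes the source as "Record of participation in exercise program 36 times".

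Section 2.5 enlarges a sample size built on completion rates: "considering a 10% dropout rate, 24 participants will be required for each group".

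**The concern.** Attendance differs from an exercise test or a questionnaire. When a patient stops coming, the remaining sessions were not attended, and the number attended is a complete observation. Non-attendance is what the trial sets out to change.

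Section 2.11 does not draw this distinction. For the two attendance outcomes, its two analysis sets differ by the patients without a 3-month evaluation, and the replacement rule is what the section offers for filling them in. It does not say when LOCF applies and when the mean, or whether the mean is taken within arm or over both arms. The count is scheduled once, at 3 months, so LOCF on scheduled visits has nothing earlier to carry forward. That makes the mean (or multiple imputation above 20% dropout) a live option for the primary analysis. With 24 patients per arm, two to four substituted values per arm are enough to matter.

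**Working it through.** **1. The plan's own figure.** Inputs from Section 2.5: 55.4% versus 15.4%, power 0.80. Alpha 0.05 is from Section 2.11; two-sided is an assumption. The average rate is 0.354.

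n = [1.96·√(2·0.354·0.646) + 0.842·√(0.554·0.446 + 0.154·0.846)]² / 0.40² = (1.326 + 0.517)² / 0.16 = 21.2, so 22 per arm, as stated. For 10% dropout, 22 × 1.10 = 24.2 and 22 / 0.90 = 24.4, against 24 stated. The sample size is not affected by this point.

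**2. What each permitted rule assigns.** Take a patient who attends k sessions and leaves. Assume, for illustration, that the planning rates are the mean share of the 36 sessions attended. Arm means are then 36 × 0.554 = 19.9 and 36 × 0.154 = 5.5, the difference is 14.4, and the pooled mean is 12.7.

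- Section 2.8.1, or LOCF on a running session count: k, the true value.
- LOCF on scheduled visits: no earlier value exists.
- Arm-specific mean: 19.9 if paid (18 or more, hence a completer), 5.5 if control (a non-completer).
- Pooled mean: 12.7 in either arm (a non-completer).
- Multiple imputation above 20% dropout: a value drawn from a model.

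**3. Type I error with arm-mean filling, missing at random.** Let d be the fraction filled. Filled values add nothing to the sum of squares but are counted in n. The estimated variance of a mean is about s²(1−d)/n, while the true one is s²/[n(1−d)]. The standard error is too small by a factor of (1−d), so the two-sided error is 2·P(Z > 1.96(1−d)).

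- d = 0.10: 2·P(Z > 1.764) = 7.8%.
- d = 0.20: 2·P(Z > 1.568) = 11.7%.

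**4. Simulation.** 40,000 trials per scenario, 24 per arm, beta-binomial attendance over 36 sessions (assumed shape). One to four patients per arm were set missing, either at random or as the lowest attenders.

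Rejection rate of the sessions t test with no true effect (range over the assumed common attendance rates):

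| Value used | 2+2 random | 4+4 random | 2+2 lowest | 4+4 lowest | 1 and 4 lowest |
|---|---|---|---|---|---|
| Actual count | 4.7-5.3% in all scenarios | | | | |
| Arm mean | 7.1-7.5% | 10.3-10.6% | 7.9-10.7% | 12.1-18.0% | up to 20.9% |
| Pooled mean | 4.6-5.3% | 4.6-5.3% | 5.5-8.0% | 6.1-10.8% | up to 15.6% |

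Difference at the planning rates, as sessions / completion points (actual 14.4 / 46):

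| Missing | Arm mean | Pooled mean |
|---|---|---|
| 2+2 random | 14.4 / 49.0 | 13.2 / 42.4 |
| 4+4 random | 14.4 / 51.6 | 12.0 / 38.6 |
| 2+2 lowest | 15.6 / 54.1 | 14.3 / 46.4 |
| 4+4 lowest | 16.6 / 62.6 | 13.8 / 46.3 |
| 1 paid, 4 control, lowest | 14.1 / 50.1 | 12.6 / 46.3 |
| 4 paid, 1 control, lowest | 17.5 / 62.6 | 15.6 / 46.4 |

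**5. Hand checks.** Pooled mean at random: 14.4 × (1 − 2/24) = 13.2 and 14.4 × (1 − 4/24) = 12.0. Arm mean with the lowest attenders missing: each paid dropout turned into a completer adds 1/24 = 4.2 points. Two give 46.4 + 8.3 = 54.7 (simulated 54.1), and four give 46.3 + 16.7 = 63.0 (simulated 62.6).

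**6. Not examined.** Multiple imputation and the Mann-Whitney alternative were not simulated. The variance argument in step 3 concerns single imputation and does not carry over to multiple imputation.

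**The case against.** A reader might infer that the plan credits every dropout with average attendance and so exaggerates the incentive effect. The documents do not support that, for these reasons:

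- No sentence says that a patient who stops attending is missing on attendance. Table 1's footnote points to a participation record, and a recorded count need not be missing.
- LOCF is named first. Section 2.6.1 ties payment to the session number, so a running tally must exist at least in the paid arm. LOCF on such a tally returns the true count.
- Section 2.8.1, applied to sessions, also gives the attended count.
- A 10% dropout allowance is routine. It may serve the per-protocol set and does not show that dropouts are treated as missing on attendance.
- The direction of bias is not fixed. A pooled mean usually dilutes the effect. An arm mean leaves the session difference unchanged if data are missing at random, and slightly lowers it (14.1 against 14.4) when more low-attending control patients are missing.

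All of this stands, and it makes the harm conditional. It does not remove the defect. The article states a rule, places it directly after the attendance tests, exempts nothing, and allows the mean as freely as LOCF. Above 20% dropout it prescribes multiple imputation for the intention-to-treat analysis with no LOCF option. This is an unsuitable stated rule, at odds with Section 2.8.1, and more than a detail left to a fuller document.

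One further objection is fair. Section 2.7 also ends participation for adverse events, recurrence and researcher decisions. Counting those sessions as not attended is a choice of estimand, and it should be stated as such.

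**Conclusion.** The point holds in conditional form. Section 2.11 permits imputation of a count that is known, for both attendance primary outcomes, and Section 2.8.1 points the other way. The same data can therefore give different primary results:

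- correct, with LOCF on a running count;
- usually diluted, with a pooled mean, which raises type I error only when missingness depends on attendance;
- too many false positives, with an arm-specific mean: about 7-8% at 10% dropout and 10-12% at 20% if missing at random, and up to 20.9% in the scenarios where the lowest attenders were missing.

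With arm means, paid dropouts may also be counted as completers while control dropouts are not, which widens the completion difference from 46 to between 49 and 63 points. That needs a paid-arm mean of at least 18 and a control mean below it, as the planning rates imply when read as mean attendance. The session effect itself is inflated only under some patterns, such as low attenders missing in equal numbers or mostly from the paid arm.

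The attendance distribution, the dropout patterns and the two-sided test are assumptions. The analytic figures of 7.8% and 11.7% need no attendance shape beyond the normal approximation. No size is claimed for multiple imputation.

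**What to change.** Add to Section 2.11, for the two attendance outcomes: *For every randomised patient whose records may be used, sessions completed is the number attended within the 3-month window according to the program's session records, including patients who withdraw or miss the 3-month visit. Sessions not attended count as not completed, patients below the completion threshold are non-completers, and no imputation is used for these two outcomes.*

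Restrict LOCF, mean and multiple imputation to the exercise-test and questionnaire values, and reword Section 2.8.1 to agree.

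The cost is one paragraph, with data taken from the program's own session records and no change in sample size. There are two downsides. The observed effect may be less favourable than with imputed sessions. Stops for medical reasons also count as non-attendance, which a prespecified sensitivity analysis can address.
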